
### Clinical data analysis

According to the study data, the effect indices of the two groups will be calculated and compared to analyse the influence on the prognosis of PDPN. Indices of scales will be analysed by repeating measurement analysis of variance. The main analytical indicators will be the curative effect index and recurrence rate. A *t* test will be used for measurement data with a normal distribution. The Wilcoxon rank sum test will be used for nonnormal distribution; the Pearson chi-square test will be used for counting data. If it is a sequential concatenation table, the CMHX^2^ test will be used.

The measurement data of different treatment groups will be statistically described by the mean ± standard deviation (‾*χ* ± s). Intragroup differences will be assessed using a t-test at baseline; analysis of variance (ANOVA) will be used to compare measurement data at different stages; and SNK will be used for pairwise comparisons. Changes between groups before and after treatment will be analysed by ANOVA. If the data do not fit the above statistical analysis conditions (such as nonnormal), a nonparametric test will be used.

Counting data from different treatment groups are statistically described by frequency (constituent ratio). Changes between groups before and after treatment will be tested using the X2 test (CMHX2 test) or nonparametric test. The analysis of data results from participants not complying with the study protocol will be treated according to statistical analysis with randomization and multiple interpolation.

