#### Short-Form McGill Pain Questionnaire

The Short-Form McGill Pain Questionnaire is a high-quality tool used to evaluate neuropathic and nonneuropathic pain conditions [29]. It provides basic information for pain research. The questionnaire will be administered at baseline, the 1st, 2nd, 3rd and 4th weeks of the treatment period, and at the 1-, 2-, 3- and 6-month follow-ups after treatment.

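### Between-arm change is analysed without baseline adjustment, which is unbiased but inefficient, and SNK is named for pairwise comparisons although it does not control family-wise error with four or more means

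*Protocol article*

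**What the plan says.** All the methods at issue stand in the protocol article under Clinical data analysis.

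- Between-arm change: "Changes between groups before and after treatment will be analysed by ANOVA".
- Continuous measurements generally: "A *t* test will be used for measurement data with a normal distribution", with a rank sum test otherwise.
- Scale scores: "Indices of scales will be analysed by repeating measurement analysis of variance".
- Comparisons over time: "analysis of variance (ANOVA) will be used to compare measurement data at different stages; and SNK will be used for pairwise comparisons".

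No covariate is named for any of these. The Short-Form McGill is scheduled at "baseline, the 1st, 2nd, 3rd and 4th weeks of the treatment period" and "at the 1-, 2-, 3- and 6-month follow-ups after treatment", which makes 5 + 4 = 9 assessments. The BPI has the same schedule. The MNSI, NPSI, LANSS and blood measures are taken at baseline and week 4 only. For SCV and CPT, the Neurophysiological index section can be read as measurement after every treatment session or once after the course.

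The Sample size calculation section bases the trial on average change in the Short-Form McGill, with 24 per group before attrition.

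**The concern.** There are two separate issues.

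**Baseline.** A change score subtracts the whole baseline value, whatever its correlation with follow-up. A t test on the final value ignores baseline. ANCOVA estimates the weight from the data, so in large samples it is at least as precise as either. With 24 to 30 per arm, that precision is worth having.

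**SNK.** SNK tests ordered means in steps. Once a wide range is declared different, each narrower range is tested at the full 5%. If several subsets of truly equal means lie apart from each other, each subset brings its own 5% chance of a false claim. The plan attaches SNK to comparisons across stages, where the Short-Form McGill and BPI have nine means. Statements about which visits differ would then carry more error than the nominal level suggests.

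**Working it through.** **1. The plan's own sample size.** Inputs from Sample size calculation: mean difference 0.81, SD 0.07, non-inferiority limit −0.1, alpha 0.025, power 0.80. With n = 2(1.96 + 0.84)² × SD² / (difference)²:

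- Non-inferiority, true difference 0.81: distance to the limit 0.91, n = 1 per group.
- Non-inferiority, true difference 0: distance 0.1, n = 8.
- Superiority with 0.81 and SD 0.07: n = 1.
- Superiority with 0.81 as a standardised effect (SD 1), two-sided 5%: 15.70 / 0.656 = 23.9, so n = 24.

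Of the readings tried, only the last gives the stated 24. The attrition step reproduces: 24 / 0.8 = 30, and 5 × 30 = 150. The failure of the stated inputs to give 24 is a separate matter. Here it means only that 0.81 as a standardised effect on the change scale is an assumption, not a figure the article gives.

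**2. Gain from baseline adjustment.** Let SD be σ at both times and rho the correlation. The article gives no rho, so 0.3, 0.5 and 0.7 are assumed.

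- Change-score variance: 2σ²(1 − rho).
- ANCOVA residual variance: σ²(1 − rho²).
- ANCOVA relative to change: (1 + rho)/2.
- ANCOVA relative to final-value t test: 1 − rho².

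| rho | ANCOVA / change | ANCOVA / final value | Effect 0.81/√((1+rho)/2) | Power at 24 per arm |
|---|---|---|---|---|
| none (change score) | 1 | – | 0.81 | 78.4% |
| 0.3 | 0.65 | 0.91 | 1.00 | 92.6% |
| 0.5 | 0.75 | 0.75 | 0.94 | 88.7% |
| 0.7 | 0.85 | 0.51 | 0.88 | 84.6% |

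Power uses the exact noncentral t with 46 degrees of freedom, two-sided 5%. The one degree of freedom spent on the covariate is ignored. Put as sample size, 24 per arm becomes 24 × 0.65 = 15.6 (16), 24 × 0.75 = 18, or 24 × 0.85 = 20.4 (21).

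**3. SNK error rate.** In the worst configuration the means form m equal pairs that lie far apart, and the family-wise error is 1 − 0.95^m.

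| Means | m | Formula | Simulated (24 per mean, independent) |
|---|---|---|---|
| 3 | 1 | 5.0% | 4.8% |
| 4 | 2 | 9.75% | 9.5% |
| 5 | 2 | 9.75% | 9.9% |
| 9 | 4 | 18.5% | 17.9% |

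Nine correlated stages (within-person correlation 0.5) with a repeated-measures error term simulate at 18.3%; a run with 30 participants gave 19%. When all means are equal the rate stays near 5% (4.9% for four means, 4.8% for five). With two means there is one comparison and no inflation.

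**4. Error term.** The sentence that names SNK does not say which error term it uses. If a one-way ANOVA term were applied to nine correlated stages, the full-null rate in simulation at correlation 0.5 would fall to 0.03% to 0.1%, because within-person correlation is ignored. The text is open on this, so it is a reason to state the error term, not a demonstrated fault.

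**The case against.** **The planned comparison is valid.** This stands. Randomisation makes the unadjusted difference unbiased, and a change score does use baseline, only with a fixed weight. The loss is in precision.

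**An article may leave covariates to an analysis plan that is not shown.** This stands in part. If that plan adjusts for baseline, the first half of the point falls away. But the article does name its methods, and as named they are unadjusted.

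**The SNK figures are worst cases.** True. They need several exactly equal pairs set well apart, and the rate is near 5% when nothing differs. But a procedure chosen for pairwise comparisons should hold its level in those cases too, and Tukey and Holm do.

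Three stronger readings are tempting and are not supported:

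- *That incomplete participants are simply dropped.* Classical repeated-measures ANOVA does need complete cases, and Participant elimination criteria lists incomplete data as a ground for removal. But Treatment of participant discontinuation uses the last available result, and Clinical data analysis ends by naming what appears to be multiple imputation for those who do not comply. The three statements conflict; none can be taken as the rule.
- *That the main contrast is diluted over visits.* The plan separately provides a before-and-after comparison between groups, and repeated-measures ANOVA ordinarily gives an arm-by-visit test.
- *That all pain scales have nine time points.* Only the BPI and Short-Form McGill do.

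**Conclusion.** The point holds in two limited respects and merits a change, but it does not make the planned comparison invalid.

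First, leaving out baseline costs precision. The variance could be 15% to 35% lower than for change scores, for assumed rho of 0.7 to 0.3 and equal variance at both times. The matching power figures, 78% against 85% to 93%, rest on the further assumption that 0.81 is a standardised effect. At the article's literal SD of 0.07 the ratio is 0.81 / 0.07 = 11.6, and power is essentially 100% either way.

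Second, SNK does not protect the family-wise error with four or more means: up to about 10% for five and 18% to 19% for nine. A reader might infer that this reaches the randomised comparison of electroacupuncture with sham in PDPN. It does not, because that comparison has two means. The inflation concerns comparisons across stages or across several groups.

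**What to change.** Make these changes in the analysis plan before the database is locked:

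1. For measures taken at baseline and week 4 (blood measures, NPSI, LANSS, MNSI), use ANCOVA on the week-4 value with baseline as covariate. Apply the same to SCV and CPT once their schedule in Neurophysiological index is clarified.
2. For BPI and Short-Form McGill, use a mixed model on the eight post-baseline visits with baseline score, arm, visit and arm-by-visit, and report the electroacupuncture-minus-sham difference at week 4 within PDPN. The article does not name week 4 as the main contrast, so state it. An unstructured covariance has 8 × 9 / 2 = 36 parameters for 60 participants, so name a simpler fallback.
3. Replace SNK with Tukey or Holm, with a within-person error term wherever stages are compared.
4. Reconcile the three statements on incomplete data into one rule consistent with the models above.

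The cost is wording only. Standard software fits these models, and no visit, measurement or participant is added.

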## Discussion

Among diabetic patients, approximately 25% develop PDPN. The probability of PDPN is higher in patients with type 2 diabetes (T2DM) [36]. In PDPN, which is most often associated with sensory motor neuropathy, patients may feel burning, pricking or electric pain. Some patients may even describe hyperalgesia or abnormal pain [37, 38], which greatly reduces their quality of life. Acupuncture is a nonpharmacological treatment. It is very effective for pain relief, especially for PDPN. A Japanese study showed that 20 patients with PDPN who received acupuncture treatment had better pain relief than the patients in the drug treatment group [39]. Another study confirmed that acupuncture can effectively improve the main symptoms of patients with PDPN, significantly reducing or even ending drug use [40]. There is still a lack of clear reporting on the mechanism of acupuncture in the treatment of PDPN. Acupuncture can act on all parts of the central nervous system, and it can exert analgesic effects by regulating neurotransmitters and signalling pathways and immune responses [41]. Using multimodal cerebral imaging technology, Zhou [42] found that electroacupuncture at Weizhong (BL40) and Dachangshu (BL25) can change the cerebral function pain centre and cerebral default network. Therefore, this clinical trial aims to determine whether acupuncture can improve the state of cerebral central sensitization in patients with PDPN. We will use rs-fMRI to better explore the neuroregulatory effect of acupuncture on PDPN cerebral central sensitization and to improve the overall efficacy of acupuncture.

To date, high-quality clinical evidence for acupuncture in PDPN is still insufficient because most clinical trials have had small sample sizes, short or nonexistent follow-up or other unavoidable restrictions. The design of this study takes into account the placebo effects, so two sham acupuncture groups will be set up for comparison. To avoid deviations in the results and improve the reliability of the clinical data, we will try to maintain the consistency of the baseline. Participants will be strictly selected according to the inclusion and exclusion criteria. The rs-fMRI of all participants will be carried out in the MRI room of Guang’anmen Hospital (China Academy of Chinese Medical Science). Our research will help explore the potential clinical applications of acupuncture.

## Trial status

This trial was registered with the Chinese Clinical Trial Registry (www.chictr.org.cn/) on 26 June 2019. This trial is currently in the recruitment phase. We predict that recruitment work will be finished by December 2021.

## Data Availability

Not applicable.

## Abbreviations

DM: Diabetes mellitus
DPN: Diabetic peripheral neuropathy
PDPN: Painful diabetic peripheral neuropathy
rs-fMRI: Resting-state functional magnetic resonance imaging
DTI: Diffusion tensor imaging
MRS: Magnetic resonance spectroscopy
MNSI: Michigan Neuropathy Screening Instrument
NPSI: Neuropathic Pain Symptom Inventory
LANSS: Leeds Assessment of Neuropathic Symptoms and Signs
BPI: Brief Pain Inventory
